## **I. CONTINUED FOLLOW-UP OF WEEK 20 RESPONDERS**

I.1. Eligibility for continued treatment at week 24:

I.1.a. Patients who have a virologic response (undetectable HCV RNA as determined by the Central Virology lab) at week 20 will be treated through week 48 and follow-up through week 72. If virologic breakthrough or relapse is documented by detection of HCV RNA at weeks 36, 48, 60 or 72, patients will be considered for randomization (Section J). Any virologic breakthrough or relapse must be confirmed by a blood draw on a separate day. When a patient has had two detectable HCV RNA tests (as determined by the Central Virology lab) s/he will be offered enrollment into the Randomization Phase.

I.2. Treatment discontinuation:

Patients will be discontinued from treatment at Week 24 and at any point thereafter if they develop any of the criteria listed in Section L.

I.3. Patient Visits:

I.3.a. Will occur every 6 weeks until Week 48, as well as at Week 60 and Week 72.

I.3.b. Blood will be drawn and questionnaires will be completed at each visit according to schedule in Table 3.

I.4. Management:

I.4.a. Study drugs will be continued for a total of 48 weeks.

I.4.b. Medication management will be at the Principal Investigator's discretion.

## **J. RANDOMIZED PHASE**

### **J.1. Assessment for Randomization**

J.1.a. Patients who do not have a virologic response may be assessed for randomization at the following times:

1. between weeks 20 and 24 for those who have gone through the Lead-in Phase,
2. during Screening for the Express patients,
3. at weeks 36, 48, 60 or 72 for Week 20 Responders. Any virologic breakthrough or relapse must be confirmed by a blood draw on a separate day. Patient must be willing to be re-biopsied if their baseline (Screening) biopsy is greater than 30 months from the time of Breakthrough/Relapse Randomization.
4. After Week 72, a W20 Responder HALT-C patient who relapses may be re-screened as an Express patient.

J.1.b. The investigator will confirm the patient's eligibility for randomization, as follows:

1. A serum sample will be drawn and sent to the Virology Core Laboratory (via the Central Repository) for determination of HCV RNA.
2. AFP determination and Ultrasound examination of the liver will be performed for HCC Screening.
3. Laboratory tests, including liver chemistries, routine chemistries, CBC, TSH, and PT will be obtained.
4. Calculation of Child-Turcotte-Pugh score.
5. Willingness to participate in the trial for 4 years after randomization.

J.1.c. Patients with detectable HCV RNA at weeks 20, 36, 48, 60 or 72 and during Screening for Express patients will not be eligible for the Randomized Phase if they have any of the following:

1. elevation of serum alpha-fetoprotein greater than 1000 ng/mL
2. evidence of HCC on ultrasound
3. Child-Turcotte-Pugh score greater than or equal to 7 at 2 consecutive visits:
  - week 12 and week 20 for those patients entering through the Lead-in Phase
  - 2 separate Screening visits for Express patients
  - Weeks 36, 48, 60, 72 for Week 20 Responders
4. unwillingness to repeat a baseline (Screening) biopsy which is greater than 30 months from time of Breakthrough/Relapse Randomization. This biopsy must be read by the Central Pathology for stratification of Randomization.

Patients who discontinue peginterferon alfa-2a treatment during the Lead-in Phase or during treatment in the parallel responder protocol are not eligible to be randomized. (see L.3.)

J.1.d. Prior to randomization, patients will be stratified on the basis of the presence or absence of cirrhosis, as determined by central reading of baseline (Screening) biopsy. Breakthrough/Relpase patients will be stratified on the basis of the central reading of the most recent liver biopsy. Patients will not be excluded if the central reading of their biopsy is less than fibrosis stage 3

J.1.e. All eligible patients will be randomly assigned to one of two groups as follows:

1. To continue treatment with peginterferon alfa-2a alone at a dose of 90 µg administered once weekly for an additional 42 months.

If a patient entering the Randomized Phase has been on 45µg peginterferon alfa-2a, a dose increase back to 90µg may be made at the Principal Investigator's discretion, but is not mandatory.

2. To stop peginterferon alfa-2a/ribavirin therapy and be followed prospectively for an additional 42 months without treatment.
- 3.

J.1.f. G-CSF or GM-CSF may not be used in the Randomized Phase.

J.2. Follow-up schedule:

All patients, in both arms of the study, will be seen at regular intervals, examined and undergo various laboratory studies as defined in Table 2. Results of these tests and procedures may be shared with the patient.

In the event that a patient who is randomized cannot/will not complete all of the scheduled study visits, the patient will be offered HCV-RNA testing, an ultrasound, a liver biopsy and endoscopy at their last study visit, if deemed appropriate by the PI, in addition to all regularly scheduled tests and procedures. Every effort will be made to continue collecting any data possible on all patients who have been randomized.

J.3. Liver biopsy:

All patients will undergo repeat liver biopsy at study visit month 24 and study visit month 48 regardless of treatment group.

Only percutaneous biopsies will be performed. Patients with a prothrombin time > 1.5 INR or platelet count < 50,000 will not be biopsied.

J.4. Post-treatment follow-up:

Patients in both groups will be followed, but not treated, for an additional 6 months after study visit Month 48 (Table 2, study visit Month 54). Additional follow-up visits will be offered to patients at Month 60 and Month 72 until April 2007. After April 2007 follow-up visits every six months will be offered to all patients who are being currently followed in the Main Trial except for those patients who have undergone liver

transplantation.

J.5. Endoscopy:

An endoscopy will be performed within 4 weeks of the randomization visit if the patient has not had an endoscopy performed within the past 12 months.

**K. OUTCOME VARIABLES**

K.1. Primary Outcome Variables

The major outcome variable used in this study will be progression of liver disease as judged by any of the following outcomes:

K.1.a. Increase in Ishak fibrosis score by 2 points or more at 2 or 4 year biopsies

K.1.b. Death from any cause

K.1.c. Development of HCC

K.1.d. CTP score of 7 or higher at two consecutive study visits

K.1.e. Variceal hemorrhage

K.1.f. Ascites

K.1.g. Spontaneous bacterial peritonitis

K.1.h. Hepatic encephalopathy

K.2. Secondary Outcome Variables

Secondary outcome variables will include:

K.2.a. Quality of life,

K.2.b. Serious adverse events, and

K.2.c. Events requiring dose reductions (in both treatment groups).

K.2.d. Changes in fibrosis from baseline at year 2 or year 4 biopsy.

K.2.e. Presumed Hepatocellular Carcinoma

**L. CESSATION OF TREATMENT**

L.1. Outcomes which require permanent discontinuation of treatment:

L.1.a. Death from any cause

L.1.b. Liver transplant

L.1.c. HCC

L.1.d. UNOS Status 2b as defined by the 1999 UNOS Transplant Criteria Meeting:

1. Presence of a small hepatocellular carcinoma; or
  2. CTP score of 10 or more; or
  3. CTP score of 7 or more plus any of the following:
    - Documented unresponsive variceal hemorrhage
    - Hepatorenal syndrome
    - Occurrence of one episode of spontaneous bacterial peritonitis
    - Refractory ascites unresponsive to treatment
- L.2. By these criteria, onset of ascites, variceal hemorrhage, or hepatic encephalopathy do not require discontinuation of peginterferon alfa-2a but may lead to withholding further therapy if, in the opinion of the investigator, continuation is not in the patient's best interest.
- L.3. Randomized patients who stop receiving peginterferon alfa-2a will continue to be followed at regular visit intervals for the duration of the trial (if possible). Patients who discontinue treatment during the Lead-in Phase will not be followed beyond 24 weeks except for follow-up on all unresolved adverse events.

## **M. DOSE MODIFICATION:**

### **M.1. Peginterferon alfa-2a dosing:**

#### **M.1.a. Factors that will lead to a reduction in the dose of peginterferon alfa-2a include:**

1. Disabling symptoms, which, in the opinion of the investigator, are related to peginterferon alfa-2a treatment and prevent the patient from performing his/her occupation or daily tasks.
2. A rash consistent with allergic reaction or vasculitis.
3. Reductions in the platelet count according to the guidelines in Appendix D4 (page 67).
4. A reduction in neutrophil count according to the guidelines in Appendix D4 (page 67).
5. Any adverse reaction, which, in the opinion of the investigator, places the patient at increased risk.

#### **M.1.b. The dose of peginterferon alfa-2a may be reduced as follows:**

There are 3 prescribed levels for dose reduction:

- 135 µg
- 90 µg
- 45 µg

During the randomized phase 90µg may be reduced to 45 µg for cytopenias or other side effects. Peginterferon alfa-2a can be increased to 90µg at the investigator's discretion.

Please refer to Appendix D4 (pages 65 - 70), peginterferon alfa-2a Dose Adjustment Guidelines for complete information on dose adjustments.

M.1.c. Once a patient's dose has been decreased, the investigator may attempt to increase the dose back to or toward the previous stable level only if the following conditions are satisfied:

1. the event or circumstance responsible for the dosage adjustment has resolved or improved;
2. the patient has been at the lower dose for  $\leq 4$  consecutive doses;
3.  $\leq 6$  total doses have been administered to the patient at the lower level during the entirety of the treatment period. As a guideline, patients who have received more than 4 consecutive or 6 total doses of peginterferon alfa-2a at the lower dose level should not have their dosage regimen readjusted upward. If 4 or more consecutive doses of peginterferon alfa-2a are held or otherwise not administered (i.e., the patient has not received test medication for more than 28 days), the patient should be considered intolerant of the test medication or non-compliant, whichever is more appropriate to the clinical situation. In such cases, the investigator should consider discontinuation of study medication.

M.1.d. Every attempt will be made to keep those patients randomized to treatment with peginterferon alfa-2a on therapy by dose reduction.

M.2. Ribavirin dosing:

M.2.a. The dose of ribavirin will be reduced during the Lead-in Phase as follows:

If either of the following is confirmed: (1) a patient *without* significant cardiovascular disease experiences a fall in hemoglobin to  $<10$  g/dL and  $\geq 8.5$  g/dL or (2) a patient *with* stable cardiovascular disease experiences a fall in hemoglobin by  $\geq 2$  g/dL during any 4 weeks of treatment, the ribavirin dose should be reduced to 600 mg per day (200 mg in the morning and 400 mg in the evening). Further reductions may be considered.

Patients who have more than a 3 g/dL decrease from baseline in their hemoglobin concentration should have consideration given to an appropriate work-up for anemia, including reticulocyte count, search for sources of bleeding, etc., especially if a further drop occurs following some weeks of apparently stable hemoglobin levels on ribavirin.

M.2.b. If a patient cannot tolerate ribavirin, then he or she can be treated with peginterferon alfa-2a alone and randomized, providing eligibility criteria are met. Ribavirin should be discontinued under the following circumstances:

1. If a patient without significant cardiovascular disease experiences a fall in hemoglobin confirmed to be less than 8.5 g/dL.
2. If a patient with stable cardiovascular disease maintains a hemoglobin value  $<12$  g/dL despite 4 weeks on a reduced dose [21].

In the event of ribavirin being discontinued, it can be reintroduced at a daily dose of 600 mg and increased thereafter at the investigator's discretion. In the event of ribavirin being reduced, it can be increased at the investigator's discretion. It is not considered necessary to tailor the reduced dosing according to the 75 kg cut-off level.

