## **H. LEAD-IN PHASE:**

All patients who meet and completely fulfill study criteria at both screening visits are eligible to enter the Lead-in Phase of this trial except eligible Express patients who will enter the Randomized Phase of this trial. (Section J)

H.1. Baseline visit:

H.1.a. The baseline visit should be held within 14 weeks of screening visit #1.

H.1.b. Baseline data will be obtained as shown in Table 1.

H.1.c. Instructions and study medications will be distributed to patients.

H.1.d. All patients who have neutrophils  $>1,500/\text{mm}^3$  and platelet count  $>75,000/\text{mm}^3$  will initially be treated for 24 weeks with peginterferon alfa-2a180  $\mu\text{g}$  once weekly plus ribavirin 1000-1200 mg (prescribed according to weight  $<75\text{kg}$ ,  $>75\text{kg}$ ) daily in two divided doses. Patients previously intolerant to ribavirin may receive peginterferon alfa-2a alone, at the discretion of the site investigator.

H.1.e. Patients who are admitted to the study with platelet count from  $50,000/\text{mm}^3$  up to  $75,000/\text{mm}^3$  and/or neutrophils between  $1,000/\text{mm}^3$  to  $1,500/\text{mm}^3$ , can be enrolled but the following special precautions will apply:

Safety measures for patients with platelet count under  $75,000/\text{mm}^3$  and/or neutrophils under  $1,500/\text{mm}^3$

1. The ribavirin dosage may be unchanged or lowered at the PI's discretion. Patients will start at a reduced dose of 90  $\mu\text{g}$  of peginterferon alfa-2a once weekly.

2. Patients will be monitored more closely with the addition of a CBC with differential at Week 1 and Week 6.
3. Patients will be asked to hold weekly dose of peginterferon alfa-2a until the results of the CBC with differential are assessed by the PI.
4. The first 25 patients entering the Lead-in Phase with a lowered platelet and/or neutrophil count will have ongoing monitoring by the DSMB for the first 8 weeks of treatment.
5. A separate dose reduction scheme will be followed for these patients (see Appendix D, Table c).
6. Dose adjustment upwards of peginterferon alfa 2-a should be made at the discretion of the PI after 8 weeks in the Lead-in.

H.1.f. G-CSF or GM-CSF may not be used in the Lead-in Phase.

H.2. Weeks 2-20.

During this lead-in treatment phase all patients will be seen and examined at regular intervals, and will undergo various laboratory studies as defined in Table I.

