| <20,000                                          | Stop Drug                                                                            |

| ANC
(cells/mm^3) | Downward Dose Adjustment                                        |
|---------------------------------------|------------------------------------------------------------------------|
| ≥750                                  | None                                                                   |
| 250 - 750                             | Delay or hold dose until ≥750 then resume dose with 1 Level adjustment |
| <250                                  | Stop Drug                                                              |

Safety measures for patients with platelet count under 75,000/mm^3 and/or neutrophils under 1,500/mm^3:

1. The ribavirin should be unchanged but may be lowered at the PI's discretion. Patients will start at a reduced dose of 90 µg of peginterferon alfa-2a once weekly.
2. Patients will be monitored more closely by adding a CBC with differential blood tests at Week 1 and Week 6.
3. Patients will be asked to hold weekly dose of peginterferon alfa-2a until the results of the CBC with differential blood test are assessed by the PI.
4. Patients entering Lead-in with a lowered platelet and/or neutrophil count will have ongoing monitoring by the DSMB for the first 8 weeks of treatment.
5. A separate dose reduction scheme will be followed for these patients as indicated in Table c above.
6. Dose adjustment upwards is at the discretion of the PI after 8 weeks in the Lead-in.

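### Read literally, M.2 gives Lead-in patients whose cardiovascular disease is both stable and significant no stand-alone hemoglobin value at which ribavirin should be reduced or stopped

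*Protocol*

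**What the plan says.** Four rules in M.2 tie the ribavirin dose to hemoglobin, and they divide patients by cardiovascular status.

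| | Without significant cardiovascular disease | With stable cardiovascular disease |
|---|---|---|
| Reduce to 600 mg/day (M.2.a) | Confirmed value below 10 and at least 8.5 g/dL | Confirmed fall of at least 2 g/dL during any 4 weeks |
| Stop (M.2.b) | Confirmed value below 8.5 g/dL | Value stays below 12 g/dL after 4 weeks on a reduced dose |

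The reduction for the right-hand column applies when a patient with "stable cardiovascular disease experiences a fall in hemoglobin by" 2 g/dL or more. The stop for the left-hand column reads "If a patient without significant cardiovascular disease experiences a fall in hemoglobin confirmed to be less than 8.5 g/dL". The stop for the right-hand column begins "If a patient with stable cardiovascular disease maintains a hemoglobin value" and carries the condition "despite 4 weeks on a reduced dose".

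The rest is advice or discretion. M.2.a says that further reductions may be considered, and adds: "Patients who have more than a 3 g/dL decrease from baseline in their hemoglobin concentration should have consideration given to an appropriate work-up". M.2.b offers a tolerance route: "If a patient cannot tolerate ribavirin, then he or she can be treated with peginterferon alfa-2a alone and randomized". For patients who enter with low platelets or neutrophils, H.1.e says "The ribavirin dosage may be unchanged or lowered at the PI's discretion", and Appendix D4 says "The ribavirin should be unchanged but may be lowered at the PI's discretion". None of these gives a hemoglobin value for a dose change.

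**The concern.** M.2 clearly means to be more careful with cardiovascular patients: it gives them an earlier, relative trigger and a higher stop value (12 against 8.5 g/dL). But every trigger in their column depends either on the rate of fall or on a reduction already made. At the lowest hemoglobin values, the written rules then ask for less in this group than in patients at lower cardiac risk.

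What is at stake is safety in the Lead-in. B.5 names hemolysis and anemia from ribavirin as an increased risk in cirrhosis. F.17 excludes only serious cardiac disease that the investigator thinks would preclude treatment, so stable disease can enter, and F.6 admits hemoglobin down to 11 g/dL. Express patients skip the Lead-in, and I.4.b leaves the medication of Week 20 responders to the Principal Investigator.

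**Working it through.** The plan states no figure to reproduce. The check applies the four rules and the work-up note, as written, to hemoglobin courses at the Table 1 CBC visits (baseline, weeks 2, 4, 8, 12, 16, 20, 24). All hemoglobin values are assumptions, and each is taken as confirmed. The largest fall is taken over all pairs of values at most 4 weeks apart.

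**Slow fall.** Weeks 0, 2, 4, 8: 11.5, 10.6, 9.6, 8.4 g/dL.
- Falls over 4 weeks: 11.5 − 9.6 = 1.9 and 9.6 − 8.4 = 1.2. The largest is 1.9, under 2.
- Stable and significant disease: no reduction, so the 4 weeks on a reduced dose never begin and the 12 g/dL stop cannot apply. Total fall 11.5 − 8.4 = 3.1, so the work-up note applies at week 8.
- Without significant disease: reduce at week 4 (9.6), stop at week 8 (8.4).

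**Slow fall with plateau.** Weeks 0, 2, 4: 12.5, 11.6, 10.7; then 9.5 from week 8 to week 24.
- Falls over 4 weeks: 1.8 and 1.2. Total 3.0, which is not more than 3.
- Stable and significant disease: no reduction, stop or work-up note through week 24, although every scheduled value from week 2 is below 12.
- Without significant disease: reduce at week 8.

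**Rapid fall.** 12.5 at baseline, 8.4 at weeks 4 and 8 (fall 4.1).
- Without significant disease: stop at week 4.
- Stable and significant disease, week 2 value 10.6 (fall 1.9): reduce at week 4, stop from week 8, which is 4 weeks later than the other group.
- Same course with week 2 value 10.5 (fall 2.0): reduce at week 2, stop from week 6, which is 2 weeks later. The next CBC in Table 1 is at week 8.

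**Control.** 13.0, 12.1, 11.2, 11.2 at weeks 0, 2, 4, 8 triggers nothing in either group. Slow falls that stay at 10 g/dL or above are not part of this point.

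**Range.** For a steady fall of r g/dL per 4 weeks (r below 2), the highest entry value that reaches 9.9 or 8.4 by week w is 9.9 + r·w/4 or 8.4 + r·w/4. For example, 9.9 + 1.9 × 8/4 = 13.7.

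| Reached | r = 1.0 | r = 1.5 | r = 1.9 |
|---|---|---|---|
| Below 10 by week 8 | 11.9 | 12.9 | 13.7 |
| Below 8.5 by week 8 | none (10.4 is under the entry limit of 11) | 11.4 | 12.2 |
| Below 8.5 by week 12 | 11.4 | 12.9 | 14.1 |
| Below 8.5 by week 16 | 12.4 | 14.4 | 16.0 |

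Entries from 11 g/dL up to the value shown meet no dose rule for stable and significant disease. The later rows assume a fall that neither levels off nor is acted on, so they are outer limits.

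**The case against.** The case against is mainly about scope and weight, and much of it stands.

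- **The group is narrow.** M.2 does not define *stable* and *significant* as complements. A patient whose disease is stable but not significant can be read into both columns and would then have the 10 and 8.5 g/dL values. A reader might infer that every patient with stable disease lacks them; the text supports this with certainty only where the disease is also significant.
- **The rules are not absolute.** The operative verbs are *should*, for the other group as well. It would go too far to call that group's values mandatory, or to say that M.2 requires ribavirin to continue at 8.4 g/dL. It forbids no earlier action.
- **The scheme is not reversed overall.** A fall from 14 to 12 g/dL within 4 weeks leads to a reduction only in the cardiovascular group. What is missing is a backstop at low values.
- **The work-up note covers much of the lowest range.** Anyone who enters at 11.5 g/dL or more and drops below 8.5 has fallen more than 3 g/dL. Only entries of about 11.0 to 11.4 can reach 8.4 without it. But the note leads to consideration of a work-up, not to a dose change.
- **The courses lie close to the thresholds.** This is true of the 1.9 and 1.8 g/dL falls, and it is why the delay after a rapid fall is given as 2 to 4 weeks. The range table shows that the slow-fall gap also exists at 1.0 and 1.5 g/dL per 4 weeks.
- **It may be late.** By A.2, randomized treatment ends in January 2007 and follow-up runs to October 2009; by E.8, the extension offers no medication. The Lead-in may be complete, so a change might reach few or no patients.

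None of this supplies a hemoglobin value for the group concerned.

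**Conclusion.** The point holds in this limited form, as a gap in a stated safety rule. It rests on the literal reading of M.2, on disease that is both stable and significant, and on assumed hemoglobin courses. With falls under 2 g/dL in every 4 weeks, hemoglobin can pass below 10 and 8.5 g/dL with no specified dose action. The number of such patients and the frequency of such courses are not in the protocol.

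A reader might go on to suspect bias in the trial's result. The documents do not support that: the rule governs ribavirin in the Lead-in, before randomization, and a patient who goes on with peginterferon alone can still be randomized if otherwise eligible. Sample size and primary analysis are untouched.

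**What to change.** In M.2, apply the reduction at a confirmed value below 10 g/dL and the stop at a confirmed value below 8.5 g/dL to all patients. Keep the reduction for a fall of at least 2 g/dL in 4 weeks, and the stop for values still below 12 g/dL after 4 weeks on a reduced dose, as additional triggers for stable cardiovascular disease. This also removes the *stable*/*significant* ambiguity for the two values.

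The wording change is short and needs no new tests, because Table 1 already schedules the CBCs. The costs are some extra ribavirin reductions or stops in this subgroup (number unknown) and approval under Q.2 by the Steering Committee, NIDDK, the center IRBs and the DSMB. If no patient remains in the Lead-in, the change matters only where the dosing text is used again.
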